### Study population

Two hundred and fourteen first time mothers will be cluster randomised to a sleep psychoeducation intervention compared with a booklets only group (control). Women will be in their third trimester of pregnancy when recruited and will participate until 10 months after delivery. Fathers/partners will also be encouraged to attend the sleep intervention; however, women will not be excluded if their partners do not take part. Whether or not partners attend will be recorded. The inclusion criteria require participants speak sufficient English and do not have a history of major depression. Ethical approval was granted by the Ethics Review Committee of Sydney South West Area Health Service Sydney and is registered with the Australian New Zealand Clinical Trials Registry (ACTRN12611000859987).

### Data collection

Participants will have the option to complete their questionnaires either on paper or via the internet. Those who complete their questionnaires online will be allocated a unique link that will automatically save their questionnaires to the study’s secure server. They will be informed of their link at each time point. At the 6 weeks following delivery time point, additional data collection in the form of a phone call will occur. If participants have not completed their questionnaires within 2 weeks, they will be sent a reminder email. If another week passes and data has not been received, a second email will be sent. If participants still do not complete their questionnaires, they will receive a call from the research coordinator who will collect their data over the phone. There will be an option for the participants to fill in their sleep diaries through a mobile app which is user friendly and similarly confidential.

## Materials

The Baseline questionnaires include:

1. Pittsburgh Sleep Quality Index (PSQI)

2. Insomnia Severity Index (ISI)

3. Multidimensional Assessment of Fatigue (MAF) scale

4. Epworth Sleepiness Scale (ESS)

5. Edinburgh Post Natal Depression Scale (EPDS)

6. Depression, Anxiety and Stress Scale (DASS)

7. Brief Coping Scale (COPE)

8. The General Self-Efficacy Scale (SES)

Post-delivery questionnaires include the baseline questionnaires as well as the questionnaires listed below:

9. Infant characteristics questionnaire (ICQ)

10. General feeding questionnaire

11. General sleeping questionnaire

12. Being a Mother & Bonding Scale – BaMB

13. Maternal sleep diary

14. Infant sleep diary

A description of all the questionnaires these can be found in Appendix: Questionnaires.

The Maternal and Infant sleep diaries are designed to record sleep hours for three consecutive days. There will be the option to complete these via a specially designed phone application instead of online for those who find it more convenient.

In the interest of efficiency and in order to minimise the number of questionnaires completed by the participants, the Brief COPE questionnaire, The Infant Characteristics Questionnaire and the General Feeding Questionnaire will not be administered at the 4 month time points. Furthermore, the 10 month time point will utilise the questionnaires related to the primary and secondary outcomes only.

An actiwatch will also be used for selected participants. An actiwatch is a wrist-like device which monitors movement above a given threshold via an accelerometer and provides data on sleep-wake patterns over a period of time [42].

### Procedure

#### Recruitment from Royal Prince Alfred Hospital (RPAH) prenatal classes

Patients attending prenatal classes at the RPAH will be approached by the study coordinator with a brief explanation of the study and the participant information sheet. Participants will be given the opportunity to provide their contact details. The study coordinator will then make contact with these individuals to explain the study more thoroughly and screen them for eligibility.

#### Recruitment from Facebook.com

In order to maximise recruitment, a Facebook page was published, facilitating participants to ‘share’ or recommend the study with other potential participants as well as allowing interested individuals to access the information and volunteer themselves as participants. The link to the active Facebook page as well as a screen shot of the page and the pictures presented on the page can be found in Additional file 1: Figure S2: *Facebook Page ‘Sleep for New Mums’.*

#### Time 1

Participants will be called by the study coordinator. The study will be explained and medical history, demographics and other relevant information will be collected. If the individuals are eligible, they will be asked to provide informed consent and complete the set of baseline questionnaires.

#### Randomisation

Envelopes have been prepared and sealed by an independent researcher. Each enveloped is labeled ‘Cluster1’ (C1), ‘Cluster2’ (C2) etc.… Once a minimum of 3 and a maximum of 10 participants have been screened and completed the *Time 1* components, they will be allocated into a cluster and an envelope will then be opened to reveal whether the participants in that cluster will receive intervention or control condition.

#### Time 2

Participants will receive a phone call from the study coordinator 3 weeks following the birth of the baby. For the intervention group, this is when potentially bad habits may start to form and as such we aim to remind the participants of the intervention and its content. For the control group, the phone call will be simply to provide support, which might otherwise vary between the groups.

#### Time 3

Six weeks after delivery, participants will be contacted by phone. The phone call will be scripted involving questions about sleep hours and patterns as well as courtesy questions about how they are managing. Participants in the intervention group will receive an additional segment of the script reminding them to look through the notes provided during the program and offering advice and support if necessary. We shall explore what has or has not been useful for them and direct them to the relevant section of their notes to review. We will also allow them to ask any questions they may have about sleep. At this stage, all participants will complete the online questionnaires once again. These questionnaires will include the baseline and post-delivery questionnaires.

#### Time 4

Approximately 4 months after delivery, participants will fill out the baseline and post-delivery questionnaires again.

#### Time 5

10 months after delivery; participants will fill out 2 questionnaires about sleep (PSQI & ISI), 2 about depression (DASS & EPDS) and the sleep and feeding questionnaires. This will conclude their participation in the study. A flowchart of the procedure can be seen in Figure 1.

**Figure 1 F1:**
[figure not shown]
Procedure flowchart.

The time points for data collection have been designed to follow common milestones in sleep pattern developments and changes. *Time 3 (6 weeks postpartum)* has been scheduled as few infants develop a consistent sleep wake pattern before this time so we will be able to explore how the mothers have managed this inconsistency as well as being able to give them guidance about what to look for over the coming weeks as the patterns do start to emerge [43]. *Time 4 (4 months postpartum)* has been scheduled as infants begin to develop the self-soothing abilities around 4 months of age [44] and it is at this time that the most rapid consolidation of sleep regulation occurs [45]. Therefore, completing the questionnaires at this time point will indicate changes when infants have a more predictable sleep wake pattern. *Time 5 (10 months postpartum)* has been scheduled for two reasons. Firstly, most infants no longer have a nutritional need for a night time feed and therefore in most instances babies should be able to sleep through the night at this stage [45]. Secondly, assessing mood at this time will ensure that the majority of participants with postnatal depression are found as most postnatal depression onset occurs by the 10^th^ month postpartum [45,46].

Two participants per cluster will be chosen to wear an actiwatch in order to collect actigraphy measures for 5 – 7 days at *Time 1* and 5 – 7 days at *Time 4*. The actigraphy measure will be an objective indicator of sleep-wake patterns and a validation of their self-reported sleep patterns. The actiwatches will be posted to selected participants with a reply-paid envelope. For practical reasons, the participants in each group whose babies have the latest due date will be asked to participate in the actigraphy study.

### Intervention

The intervention will consist of two 1.5hrs psychoeducational sessions held in the evenings at institutes connected to The University of Sydney. The first session, will focus on the sleep of the mother and the topics below will be outlined:

1. Understanding Sleep

2. Sleep changes during pregnancy

3. Adjusting to sleep disruption with parenthood

4. Expectations with becoming a parent

5. Sleep and Mood

6. Sleep during labour

7. Sleep for the first few days & weeks

8. Sleep and anxiety

9. The role of the partner

10. Understanding fatigue

11. Managing fatigue… as best you can

The second session will focus on the sleep of the baby. The topics below will be covered:

1. Foetal Sleep

2. Infant Sleep (quiet and active)

3. Baby monitors

4. How sleep needs change with age

5. How to know when your baby needs sleep

6. Basic rest & activity cycle (BRAC)

7. Helping your baby get to sleep & Soothing strategies

8. N.A.P.S. (Note time, Add 90, Play, Soothe)

9. Infant sleep 3 – 12 months

The sleep intervention contains videos of three new mothers with babies aged 6 weeks, 5 months and 6 months. These ‘real life’ mothers share their experiences of motherhood from their sleep & mood to how they learned to feed/settle their babies. A key message was the variation in their individual experiences of motherhood.

The program seeks to normalise sleep changes that occur during pregnancy and as a new mother. Further, it will encourage women to develop strategies to improve sleep when necessary. Specifically, information on the mechanisms of sleep and the importance of circadian rhythm and how this develops in newborns will be provided. Specific attention will be given to the difference between active and quiet sleep in newborns to ensure that new mothers do not mistake the transition between sleep stages and disrupt sleeping infants unnecessarily. Furthermore, we aim to clarify the many misconceptions associated with sleep and in particular, napping. Following the workshop, participants will have information of how to manage naps in order to improve daytime fatigue without disrupting their subsequent night of sleep.

The program aims to reassure women, that while they may get very little sleep in the first few weeks, infants will make changes in their sleep patterns as they develop. Hence, the sleep disturbance associated with motherhood will improve with time. During these early times, where sleep is necessarily compromised, the program will encourage women to sleep in preference to other activities, such as completing housework or socialising [47], when necessary.

Although the individuality of different infants will be emphasised, common infant signals for sleepiness and settling strategies will be discussed. As part of the educational component, the program describes common sleep patterns and milestones at different ages of the infant so that new mothers are prepared for the typical patterns of sleeping that characterise different stages of infancy. We also include interviews with new mothers to emphasize the key educational points raised.

The relationship between mood and sleep disturbance will be highlighted. The program will encourage women to enlist help from their partner, family and friends during this time.

The control group will receive booklets about babies’ sleep, managing sleep long term and relaxation strategies. These booklets will be given to the intervention groups as well.

### Statistical considerations

Power is difficult to calculate given that only one study has attempted to intervene in sleep in the pre or postnatal period. That intervention was delivered early in the postpartum period. The authors found a large effect size on both sleep duration (ES = 1.15), and depressive symptoms using the Edinburgh Postnatal Depression Scale (ES= 0.78) [39]. It is unclear whether a preventative program would achieve such large effect sizes. However, studies in individuals with insomnia attending a sleep intervention have consistently found effect sizes in the 0.4 – 0.8 range [48,49]. Hence, we chose the smallest of these effect sizes in order to be conservative. This was particularly important as the effect sizes we have taken into consideration were shown in interventions that treated people for insomnia, which one would expect to have a greater effect than a preventative program wherein the sample begins at a baseline level. The effect sizes (Cohen’s d) from past sleep programs using the sleep questionnaires of the current study (the PSQI and ISI) has ranged from 0.35 – 0.88 [50]. On the basis of these in order to achieve 80% power, based on the most conservative effect size, we would need only 41 participants per group to achieve significance at 0.05 level. However, the cluster design increases the sample size requirement according to the following formula: 1 + (*m* – 1)*ICC, where ICC is the intra-cluster correlation, (the correlation between patients’ scores within each group) and *m* is the average number of patients per group. We could not find any published studies, using the sleep measures and reporting ICCs. Therefore, we based our assumptions on ICCs reported for mood variables. Again, we could not find any for EPDS, however, Adams et al. (2004) [51] published 1039 ICCs from 31 studies and found the median value to be 0.01 for the HADS (interquartile range [IQR] 0 to 0.032, range 0 to 0.840). We aim for an average group size of 6, and to be conservative took the mean for the ICC of 0.42, requiring 2.6 times the number of participants. Therefore to ensure sufficient power to find differences on quality of life at an effect size of at least 0.4, we need 107 participants per group (n=214).

We anticipate that the support from the Royal Prince Alfred Hospital as well as the Facebook page that has been set up to accept anyone who expresses interest, will enable us to recruit a sample of 214 participants over 1.5years. We have aimed to be strategically conservative in calculating sample size.

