### Hypotheses

1. Women who receive the sleep psychoeducational intervention will have better outcomes 6 weeks, 4 months and 10 months following delivery than those who do not receive the intervention on the following primary outcomes.

(a) Sleep quality – measured by the PSQI

(b) Sleep patterns – measured by shorter night wake periods indicated by the mother and infant sleep diary

(c) Self-efficacy – measured by the general self-efficacy

2. If changes in sleep, consistent with hypothesis 1(a,b) are observed, we would also expect that women who received the intervention will have fewer depressive symptoms at 6 weeks, 4 months and 10 months postpartum than the control group.

The PSQI is our primary outcome, which is a scale consisting of itemised scores which are likely to be affected differentially by pregnancy and motherhood. During pregnancy, the most common causes of disrupted sleep include the need to urinate, uncomfortable position, aching in a position, and being too hot or cold [26]. These common issues predominantly contribute to Item 5 and following the birth of the baby are generally normalised or reduced. With motherhood, women are woken several times during the night by the baby’s needs, and may develop different difficulties within Item 5. Sleep tends to deteriorate or remain unchanged for women as measured by the total PSQI. We expect this intervention will improve sleep outcomes relative to the control group.

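### The sample size is said to rest on the most conservative effect size, but its target is 0.4 where 0.35 is cited for the PSQI and ISI; it names an outcome the trial does not measure, and the 80% power is not delivered as stated

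*Protocol article*

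**What the plan says.** All of the sample-size reasoning is in Statistical considerations of the protocol article. In order:

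- Sleep interventions in people with insomnia "have consistently found effect sizes in the 0.4 – 0.8 range". The next sentence reads "Hence, we chose the smallest of these effect sizes in order to be conservative".
- The text notes that treating insomnia should be expected to show a larger effect than a preventative programme.
- For the trial's own questionnaires, the PSQI and ISI, Cohen's d "has ranged from 0.35 – 0.88".
- Immediately after that range, "in order to achieve 80% power" and "based on the most conservative effect size, we would need only 41 participants per group to achieve significance at 0.05 level".
- The cluster inflation is 1 + (m − 1) × ICC, with an average cluster size of 6. The ICC evidence is a median of 0.01 with an interquartile range of 0 to 0.032, but 0.42 is adopted, with a multiplier of 2.6.
- The closing claim is 107 per group (214 in all), for "sufficient power to find differences on quality of life at an effect size of at least 0.4".

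Hypotheses states: "The PSQI is our primary outcome".

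**The concern.** Two statements do not fit the rest of the document. First, the sentence giving 41 per group follows the PSQI and ISI range and claims the most conservative effect. The smallest value cited at that point is 0.35, and it belongs to the pair of scales that includes the primary outcome, but the target at the end is 0.4. Second, the power is claimed for an outcome that is absent from Hypotheses, the primary, secondary and process outcomes, Materials and the Appendix.

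The question is what 214 participants can show. If the 80% is taken at face value for the PSQI, a null result may be read as stronger evidence against a modest effect than the sample can give. The document's own remark that prevention should do less than treatment makes the low end of the effect range the relevant one.

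**Working it through.** **Inputs** (all from Statistical considerations): power 80%; alpha 0.05; d = 0.40 (target) and d = 0.35 (lowest cited for the PSQI and ISI); m = 6; ICC 0.01, 0.032 and 0.42; 107 per group. Sidedness is not stated; two-sided is assumed unless noted.

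**1. The plan's own figure.** 41 × 2.6 = 106.6, rounded up to 107. That step reproduces. Its two factors do not.

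**2. The 41 per group.** The approximation is n = 2 (1.96 + 0.84)² / d². The two-sample t-test gives, per group:

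- d = 0.40: 99.1 two-sided (78.0 one-sided)
- d = 0.35: 129.1 two-sided (101.6 one-sided)

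With 41 per group, two-sided power at d = 0.40 is 43%, and 80% power needs d of about 0.63. One variant does give 41: a one-sided, one-sample or paired t-test at d = 0.40 (n = 40.03). That is not a comparison of two groups. Baseline adjustment would reach 41 only if 99 × (1 − r²) = 41, that is r of about 0.77, and the document states no such correlation.

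**3. The multiplier.** 1 + (6 − 1) × 0.42 = 3.1. The stated 2.6 corresponds to an ICC of (2.6 − 1)/5 = 0.32. With 3.1, the plan's own 41 would become 127.1, or 128 per group.

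**4. Power of 107 per group.** Effective n = 107 / (1 + 5 × ICC), put into a two-sided 5% two-sample t-test:

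| ICC | Design effect | Effective n per group | Power, d = 0.35 | Power, d = 0.40 | Difference |
|---|---|---|---|---|---|
| 0 | 1.00 | 107.0 | 72% | 83% | 11 points |
| 0.01 | 1.05 | 101.9 | 70% | 81% | 11 points |
| 0.032 | 1.16 | 92.2 | 66% | 77% | 11 points |
| 0.42 | 3.10 | 34.5 | 30% | 37% | 7 points |

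The normal approximation gives figures up to about one point higher.

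**5. Where the shortfall at ICC 0.42 comes from.** Taking the steps in this order:

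- With 107/2.6 = 41.2 effective per group, power at d = 0.40 is 43%, so the 41 costs about 37 points from 80%.
- Replacing 2.6 by 3.1 lowers it to 37%, about 6 points more.
- Moving to d = 0.35 lowers it to 30%, about 7 points more.

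**6. The named outcome.** The instruments listed are PSQI, ISI, MAF, ESS, EPDS, DASS, Brief COPE, SES, ICQ, BaMB, feeding and sleeping questionnaires, diaries and actigraphy. None is described as measuring quality of life.

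**The case against.** The strongest reply is that the choice of 0.4 is coherent and open. Where the protocol says it took the smallest value, the range just cited is 0.4 to 0.8, so that sentence is correct in its place. The PSQI and ISI range comes later and can be read as support for a choice already made. The closing sentence then tells the reader that the target is 0.4. This stands: a reader might infer that the first sentence is false or that the target is hidden, and the text supports neither. The inconsistency lies only in the later sentence, which claims the most conservative effect just after 0.35 has been cited.

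It can also be said that quality of life is probably a slip for sleep quality, since the Data analysis plan frames the primary hypothesis in those terms, and that no number depends on the label. That is plausible. It makes the correction editorial, but the sentence that justifies 214 still names the wrong outcome.

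Finally, a reader might infer that 107 was calculated from d = 0.4, or that the 30% power results from preferring 0.40 to 0.35. Neither is supported. A two-group test at 0.4 does not give 41, and at ICC 0.42 most of the deficit is present at d = 0.40 already.

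**Conclusion.** The point holds in this limited form. The claim to the most conservative effect conflicts with the 0.35 cited for the trial's own scales, and the power is attached to an outcome the trial does not measure. The 80% is not delivered as stated: at d = 0.35 it is missed even without clustering (72%). At d = 0.40 it is met at ICC 0 and 0.01 (83% and 81%) but not at 0.032 (77%), and it is far off at the ICC the plan adopts (37%).

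The effect-size choice is the smaller part, 7 to 11 points. At ICC 0.42 the larger part comes from 41 in place of about 99 to 100 and, to a lesser degree, from 2.6 in place of 3.1.

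These figures assume a two-sided 5% test, equal groups, clusters of exactly 6, all 107 per group analysed, and no gain from baseline adjustment or repeated measures. The documents do not settle whether enrolment should change: at d = 0.40 the requirement is about 104 per group at ICC 0.01 (99.1 × 1.05) but about 307 at ICC 0.42 (99.1 × 3.1).

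**What to change.** In Statistical considerations:

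- Replace quality of life with the PSQI.
- Either say that 0.4 is the chosen target although 0.35 has been seen with the PSQI and ISI, or delete the claim to the most conservative effect.
- Correct the 41 per group to the value for the stated effect, power and sidedness. If it rests on another method, give that method and its inputs.
- Make the multiplier agree with the stated m and ICC.
- Give the power of 214 at d = 0.35 and d = 0.40 over the quoted ICCs, as in the table above.

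Rewording alone is not enough, because 41 and 2.6 would remain wrong. The work is a few sentences and a small table. The cost is that the stated power becomes less favourable, and the sponsor has to say openly which ICC it believes.

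### The base size of 41 per group does not follow from an effect size of 0.4 at 80% power, so the stated justification for 214 does not hold

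*Protocol article*

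**What the plan says.** The reasoning is in the protocol article under Statistical considerations. It cites insomnia interventions that "consistently found effect sizes in the 0.4 – 0.8 range [48,49]. Hence, we chose the smallest of these effect sizes in order to be conservative". It adds that Cohen's d for the PSQI and ISI in past sleep programmes "has ranged from 0.35 – 0.88". The target is set with "in order to achieve 80% power", and the result is that "based on the most conservative effect size, we would need only 41 participants per group to achieve significance at 0.05 level".

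The paragraph then gives the design effect as 1 + (m – 1) × ICC, takes an average cluster of 6 and an ICC of 0.42, and states a factor of 2.6. It closes by saying that, to "find differences on quality of life at an effect size of at least 0.4, we need 107 participants per group (n=214" in total.

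It does not say whether the test is one- or two-sided, and it mentions no baseline correlation and no gain from repeated measures.

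**The concern.** Effect size, power, significance level and group size are all stated, and any three of them fix the fourth. The stated 41 is less than half of what the other three require for a simple comparison of two arms. Because the cluster inflation multiplies 41, the final size inherits the discrepancy.

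The paragraph calls its choices conservative. A reader of a null result could therefore believe that a difference of 0.4 had been sought with good power, when the calculation offered does not show this. The closing sentence also refers to quality of life, which is not among the outcomes listed; the Hypotheses section names the PSQI as the primary outcome.

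**Working it through.** **Inputs**, all from Statistical considerations: d = 0.4 (0.35 is also cited), power 80%, significance level 0.05, base n = 41, m = 6, ICC = 0.42, factor 2.6, final n = 107 per group. The cited ICC median is 0.01, with an interquartile range of 0 to 0.032. Assumptions: two-sided unless noted, equal arms, one time point, no baseline adjustment, full follow-up.

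**1. The plan's last step reproduces.** 41 × 2.6 = 106.6, rounded up to 107 per group, 214 in total.

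**2. The base figure does not.** n per group = 2 × (z for alpha + z for power)² / d².
- d = 0.4, two-sided: 2 × (1.960 + 0.842)² / 0.16 = 98.1, so 99; the t-test gives 99.08, so 100.
- d = 0.4, one-sided: 78.
- d = 0.35, two-sided: 129 (normal) or 130 (t-test).

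**3. What 41 per group delivers.**
- Power at d = 0.4, normal approximation: 0.4 × √(41/2) – 1.960 = –0.149, which gives 44%. The t-test gives 43%, or 56% one-sided.
- Power at d = 0.35, t-test: 35%.
- Difference detectable with 80% power: 0.62 (normal) or 0.63 (t-test).

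**4. The design effect.** 1 + (6 – 1) × 0.42 = 3.1, not 2.6. With m = 6, a factor of 2.6 corresponds to an ICC of 1.6/5 = 0.32.

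**5. Power of 107 per group.** Effective n = 107 / design effect; t-test, two-sided.

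| ICC (m = 6) | Design effect | Effective n per group | Power, d = 0.4 | Power, d = 0.35 |
|---|---|---|---|---|
| 0.01 (cited median) | 1.05 | 101.9 | 81% | 70% |
| 0.032 (cited upper quartile) | 1.16 | 92.2 | 77% | 66% |
| factor 2.6 as printed | 2.6 | 41.2 | 43% | 35% |
| 0.42 (as chosen) | 3.1 | 34.5 | 37% | 30% |

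By the normal approximation, 80% power at d = 0.4 holds up to an ICC of (107/98.1 – 1)/5 = 0.018.

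**6. Could an unstated gain in precision give 41?**
- Adjustment for baseline at one time point multiplies n by 1 – r². At r = 0.5 this gives 98.1 × 0.75 = 73.6, so 74 per group. Reaching 41 needs r = √(1 – 41/98.1) = 0.76.
- The mean of three follow-ups, adjusted for baseline, with equal correlation ρ throughout, multiplies n by (1 + 2ρ)/3 – ρ². At ρ = 0.5 this gives 98.1 × 0.4167 = 40.9, so 41.
- A one-sided paired or one-sample t-test at d = 0.4 gives 40.03, so 41, but that is not a comparison between arms.

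**The case against.** The best defence is that the paragraph names no test, while the Data analysis plan describes a linear mixed model with one baseline and three follow-ups. If the target were the mean of the three follow-ups adjusted for baseline, 41 per group would be exactly right at a correlation of 0.5. A condensed article might leave such detail to the full protocol.

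This stands in part: 43% is the power of an unadjusted comparison at a single time point, not of every analysis the trial might run. It does not rescue the paragraph. No such method or correlation is stated, so the origin of 41 is unknown. The Hypotheses and the Data analysis plan look for differences at 6 weeks, 4 months and 10 months, and averaging does not help a comparison at one time point. There, baseline adjustment at a correlation of 0.5 still needs about 74.

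A second defence is that 80% is attached to the 41, while 214 is said only to give sufficient power. But 107 is nothing more than 41 times the factor, so it rests on the same claim.

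In the other direction, a reader might infer that the trial has only about a coin-flip chance of finding a difference of 0.4. The documents do not support that. The low figures depend on an inflation of 2.6 or 3.1, and the ICC of 0.42 behind it lies far above the median and upper quartile that the paragraph itself cites.

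**Conclusion.** The point holds as an error in the justification, not as proof that the trial is too small. For an unadjusted comparison at one time point, two-sided at 0.05, the base should be about 100 per group; 41 gives about 43% power at d = 0.4. One-sided testing does not close the gap (78 needed, 56% power at 41).

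Carried through the plan's own chain, power for 214 is about 43% with the printed factor and about 37% with the factor that its formula gives. At the cited median or upper-quartile ICC, the same 214 women give about 81% or 77% at d = 0.4 with full follow-up. Which of these is nearest the truth depends on an ICC for the sleep measures that the article says it could not find. The Challenges section expects attrition and the sample-size paragraph makes no allowance for it, so all these figures are upper values.

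**What to change.** Keep 214 and rewrite the sample-size paragraph:

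- Replace 41 with about 100 per group (d = 0.4, two-sided 0.05, 80% power), or state the repeated-measures or baseline-correlation assumptions that justify a smaller figure and the comparison to which they apply.
- Correct the design effect: m = 6 and ICC = 0.42 give 3.1. Withdraw the 41 × 2.6 route as the basis for 214.
- Name the PSQI in place of quality of life.
- State the power of 107 per group over a stated ICC range. Unadjusted, with full follow-up and d = 0.4, it is about 81% at 0.01, 77% at 0.032 and 37% at 0.42. Say that attrition lowers these.

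The cost is a rewritten paragraph and a less favourable, more open power statement. No further participants are needed, and neither the design nor the analysis changes.

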## Methods

### Study design

This study will be a cluster randomised controlled trial. Participants will be recruited from consecutive attendees at prenatal classes at the Royal Prince Alfred Hospital (RPAH), Sydney Australia. In addition, the study is being advertised in obstetrician’s offices, and through the Study Facebook Page. Hence we will also accept self-referrals from these sources or from recommendations from friends. Participants from the same prenatal class will be randomised as a group in order to avoid contamination effects. The minimum in a cluster will be 3 and the maximum per cluster will be 10. Any participants from a group where less than 3 people consent or more than 10 people consent will join the next randomised cluster. Additional participants will join the clusters formed by the participants from RPAH based on the date they are recruited.

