### Challenges

The most significant challenge that we expect to have is recruitment and the rate of attrition. We have attempted to combine the groups as closely as possible with routine prenatal care and to offer women a range of options in how to complete the questionnaires at each assessment point. In addition, to thank women for their time in participating in the study, we will offer participants the chance to win a hamper of baby goods worth $200 upon completion of their 10 month follow up questionnaires.

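### The 107 per group does not follow from its own inputs: the design effect should be 3.1, not 2.6, 0.42 is not a mean, and the base of 41 does not fit d = 0.4

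*Protocol article*

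**What the plan says.** All the inputs are in Statistical considerations.

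- Target: the calculation is made "in order to achieve 80% power, based on the most conservative effect size". The paragraph names 0.4 as the smallest effect from insomnia interventions, and adds that the effect with this trial's sleep questionnaires "has ranged from 0.35 – 0.88".
- Base size before clustering: "we would need only 41 participants per group to achieve significance at 0.05 level".
- Inflation: the factor is 1 + (m − 1) × ICC, with m the average cluster size, set at 6.
- ICC source: no ICCs were found for the sleep measures or the EPDS, so values for mood variables were used. The cited review "found the median value to be 0.01 for the HADS (interquartile range [IQR] 0 to 0.032, range 0 to 0.840").
- ICC adopted and resulting factor: the authors "to be conservative took the mean for the ICC of 0.42, requiring 2.6 times the number of participants".
- Conclusion: "at an effect size of at least 0.4, we need 107 participants per group (n=214").

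Two other sections bear on the calculation. Study design says: "The minimum in a cluster will be 3 and the maximum per cluster will be 10". Challenges says: "The most significant challenge that we expect to have is recruitment and the rate of attrition".

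**The concern.** Formula, inputs and result are printed together and do not agree. A factor of 2.6 does not come from m = 6 and ICC 0.42. An ICC of 0.42 described as a mean sits beside a median of 0.01 and an upper quartile of 0.032. The base of 41 per group looks far too small for a two-group comparison at an effect of 0.4.

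This paragraph is the only justification given for 214 participants. If its steps fail, a reader cannot tell what effect the trial can detect. The answer runs from roughly adequate to badly short, depending on which ICC is believed, and the text does not settle which.

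**Working it through.** **Conventions.** Power is for a two-sample t-test at alpha 0.05 with equal allocation. The paragraph does not state sidedness; two-sided is assumed. Clusters are taken as equal in size, with no loss to follow-up, unless noted.

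**1. Reproducing the stated figure.** 41 × 2.6 = 106.6, which rounds up to 107 per group and 214 in total. So 107 is the base of 41 times the printed factor.

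**2. The factor.** From the printed formula, 1 + (6 − 1) × 0.42 = 3.1. To obtain 2.6 one needs either
- ICC = (2.6 − 1)/5 = 0.32 at m = 6, or
- m = 1 + 1.6/0.42 ≈ 4.8 at ICC 0.42.

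The paragraph gives neither value. Nearby choices do not fit either: m = 5 gives 2.68 (110 per group), m × ICC gives 2.52 (103.3, so 104) and 1 + m × ICC gives 3.52.

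**3. The label of mean.** (0 + 0.840)/2 = 0.42 exactly, which is the midpoint of the range. The largest mean compatible with the quoted summary puts each quarter of the values at its upper limit: 0.25 × 0 + 0.25 × 0.01 + 0.25 × 0.032 + 0.25 × 0.840 ≈ 0.22. A mean of 0.42 is impossible for that distribution.

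**4. The base of 41.** By the normal approximation, n per group = 2 × (1.96 + 0.8416)²/0.4² = 98.1, so 99; the t-test gives 99.1, so 100. One-sided it is 78. At d = 0.35, the lowest value cited for the questionnaires, the normal approximation gives 129. In reverse, 41 per group gives about 43% power at d = 0.4 and has 80% power only for d of about 0.63.

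**5. Correcting the factor alone.** 41 × 3.1 = 127.1, so 128 per group (256 in total). The effective size is 128/3.1 = 41.3 per group, which at d = 0.4 gives about 43% power. The error in the base carries through.

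**6. What 107 per group supports at d = 0.4.**

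| ICC | Where it comes from | Design effect | Effective n per group | Power |
|---|---|---|---|---|
| 0.01 | cited median | 1.05 | 101.9 | 81% |
| 0.032 | cited upper quartile | 1.16 | 92.2 | 77% |
| 0.32 | implied by 2.6 | 2.6 | 41.2 | 43% |
| 0.42 | stated | 3.1 | 34.5 | 37% |

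At ICC 0.42 the effect detectable with 80% power is about 0.68.

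**7. Sensitivity, on assumptions that are not in the article.** With 20% loss (86 per group, m held at 6), power is about 72%, 68% and 31% at ICC 0.01, 0.032 and 0.42. Cluster sizes spread evenly over 3 to 10 have a coefficient of variation of about 0.35. Using 1 + ((1 + CV²) × m − 1) × ICC with m kept at 6, the design effect is about 1.06, 1.18 and 3.4 at the same ICCs.

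**The case against.** **The slip might be in the ICC, not the factor.** Since 1 + 5 × 0.32 = 2.6 exactly, 0.42 could be a slip for 0.32. The text proves that the numbers disagree, not which one is wrong. That stands, although the exact match of 0.42 to the midpoint of the range makes 0.42 the likelier intended value. Neither reading helps: 0.32 also exceeds the cap of about 0.22 on the mean, and it leaves power at 43%.

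**The multiplier is a small part of the shortfall.** This also stands. Going from 2.6 to 3.1 moves power at d = 0.4 only from 43% to 37%. Most of the gap to 80% comes from the base of 41 combined with a very large ICC. A reader might infer that 256 participants is the right size; step 5 shows that it is not.

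**A reader might also infer that the trial is badly underpowered.** The documents do not establish this. The 37% depends on an ICC that the cited distribution does not support as typical; at the cited median the same 214 gives 81%. The opposite inference, that 214 is adequate, is not established either. The cited ICCs are for mood, none was found for the sleep measures, and power is already 77% at the upper quartile before any loss. Taking 0.01 as the base case would be a preference, and would pick the value at which 214 happens to work.

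**Attrition and unequal clusters.** A condensed article may leave a dropout allowance to the full protocol, so its absence is not counted as an error. The 20% loss and the even spread of cluster sizes are assumptions of this review. At the two low ICCs the cluster-size adjustment hardly matters.

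**Conclusion.** The concern holds as an internal error in the sample-size paragraph, at three points:

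- the design effect from the stated inputs is 3.1, not 2.6;
- 0.42 is a range midpoint and cannot be a mean of the cited ICCs;
- 41 per group does not follow from d = 0.4, which needs about 100 per group (two-sided assumed; 78 if one-sided).

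The 107 per group is therefore unsupported as derived, and scaling 41 by the correct factor does not rescue it. What 214 participants can detect depends on an ICC that the article does not know for its sleep outcomes: power at d = 0.4 runs from about 81% (ICC 0.01) to 37% (ICC 0.42), before attrition. The first two points are arithmetic on printed figures. The third and the power values rest on a two-sample comparison with equal clusters. The error lies in the stated justification and does not bias the treatment estimate. It should still be corrected, because no other basis for the sample size is given.

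**What to change.** Rewrite the paragraph for the fixed 214.

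- Remove the 41, the description of 0.42 as a mean and the factor 2.6.
- State the test, its sidedness and the effect size, then give power at d = 0.4 over a range of ICCs: about 81% at 0.01, 77% at 0.032 and 37% at 0.42 (design effect 3.1, detectable d about 0.68). Say that these are before attrition, and that the ICC source concerns mood and not the sleep measures.
- Show any follow-up rate or allowance for cluster-size variation as a labelled assumption, with the power that results.
- Do not present 128 per group (256 in total) as a corrected target.

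The cost is a rewritten paragraph and a less favourable stated power. No extra participants are needed.
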